# The relationship between different bispectral index and the occurrence of dreams in elective surgery under general anesthesia: protocol for a randomized controlled clinical trial

**DOI:** 10.1186/s13063-023-07222-2

**Published:** 2023-03-20

**Keywords:** Dreaming, Preoperative anxiety, Propofol, Satisfaction

## Abstract

**Introduction:**

Dreaming reported after anesthesia remains a poorly understood phenomenon. At present, there is a hypothesis that dreaming occurs intraoperatively and is related to light or inadequate anesthesia; thus, in order to further verify the hypothesis, we choose elective surgery under general anesthesia to observe whether the generation of dreams is related to the dose of general anesthetics maintenance.

**Methods and analysis:**

This randomized, double-blind controlled trial to observe whether the generation of dreams is related to the dose of general anesthetics maintenance in the elective surgery under general anesthesia. A total of 124 participants will be randomly allocated to a low bispectral index or high bispectral index group at a ratio of 1:1. The Hospital Anxiety and Depression Scale (HADS) is used to assess the anxiety and depression status of participants during the perioperative period. Ramsay score is used to assess patients’ sedation level after surgery in the PACU. Modified Brice questionnaire and awareness classification are used to assess whether patients experienced dreaming during the surgery.

**Ethics and dissemination:**

This randomized, double-blind controlled trial received prospective ethics committee approval at the Human Research Ethical Committee of Shengjing Hospital, Shenyang, Liaoning Province, China (Institutional Review Board registration number 2021PS664K), and was compliant with the Declaration of Helsinki. Written informed consent was obtained from all subjects participating in the trial.

## Introduction

Dreaming is a familiar and mysterious mode of cognitive function, and we involuntarily return to this mode every night. Dreaming during sleep is defined as “any type of cognitive activity that occurs during sleep” and is “a subjective experience that can only be obtained through the dreamer's memories after waking up.” Despite more than a century of scientific exploration, dreams continue to arouse the interest of sleep scientists, but they are still not fully understood [1, 2]. Moreover, its rigorous scientific exploration is a recent development, dating back to the discovery of rapid eye movement (REM) sleep in the 1950s. When this stage of sleep was first described in humans, researchers quickly noticed that people who awakened from REM sleep often reported dreaming (in 74% of cases, only 17% of non-REM [NREM] sleep). Therefore, dreaming is equivalent to rapid eye movement sleep, and this concept seems to be consistent with the electrophysiological characteristics of this sleep stage: closing the eyeballs under the eyelids, as if the sleeper is watching an animated scene [3, 4]. General anesthesia causes a drug-induced state of unconsciousness and is a non-physiological process that is similar to natural sleep. Its purpose is to create a state of sensory deprivation wherein patients are unresponsive to stimuli and thus leads to explicit amnesia [5]. Dreaming is also a common, long-lasting, and fascinating part of the anesthesia experience, but its cause and timing are still elusive. Patients usually report that they dreamed during anesthesia, but the actual time of dreaming during anesthesia is unknown. Dreaming during anesthesia can be defined as “any experience (excluding awareness) that a patient is able to recall and which he or she thinks occurred between induction of anaesthesia and the first moment of consciousness after anaesthesia” [6]. Patients receiving propofol for general anesthesia often report a higher incidence of dreaming compared with patients maintained with volatile anesthetics [7]. One explanation is that propofol and volatile anesthetics have different pharmacological effects in the central nervous system [8, 9]. Another explanation is that propofol can wake up from anesthesia faster than the volatile anesthetics, allowing patients to report their dreams before they are forgotten [10]. Why is the investigation of dreams during anesthesia important? Dreaming is one of the most common side effects of anesthesia, but it is still puzzling and requires explanation [7, 11]. Dreaming can sometimes make patients feel distressed and may reduce satisfaction with care [12]. Some patients who report dreaming worry that their anesthetic is insufficient; their experience is actually consciousness. At present, there is a hypothesis that dreaming occurs intraoperatively and is related to light or inadequate anesthesia; thus, in order to further verify the hypothesis, we choose elective surgery under general anesthesia to observe whether the generation of dreams is related to the dose of general anesthetics maintenance.

## Methods

### Participants and recruitment {10, 15}

With written informed consent, patients, aged 18–60 years and of American Society of Anesthesiologists’ physical status I–II, presenting for elective surgery during relaxant general anesthesia, were recruited. Exclusion criteria included (1) inadequate Chinese comprehension due to a language barrier, cognitive deficit, or intellectual disability; (2) diagnosis of a psychotic disorder, major affective disorder, or major drug dependence disorder; and (3) planned postoperative ventilation or anticipation of unavailability for postoperative interviews. A diagram of the trial design is provided in Fig. 1.

**Fig. 1 Fig1:**
[figure not shown]
Study flowchart

### Randomization, study intervention, and blinding {16c, 17a}

All patients were randomly divided into either the low bispectral index (LBIS) group (*n* = 62) or the high bispectral index (HBIS) group (*n* = 62). Randomization was conducted using a random-permuted block randomization algorithm. The randomization sequence was kept in sealed envelopes. On the day of surgery, the investigator opened the envelope and prepared the study drug according to the allocated group and delivered it to the operating room wrapped with opaque paper. The result of the group allocation was not opened until the time of data analysis. In all cases, anesthesia was conducted by the same anesthesiologist and outcome assessments were carried out by another anesthesiologist, and both were blinded to the group allocation. In the LBIS group, BIS was maintained between 40 and 50 during the operation, and in the HBIS group, BIS was maintained between 50 and 60 for maintenance. The patients, attending anesthesiologists, surgeons, and data collectors were all blinded to patient group assignment.

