### Standardized anesthesia

All patients were instructed not to eat for 8 h or to drink for 4 h prior to procedures, and no preoperative drugs were administered. Routine monitoring devices were set up to monitor electrocardiogram, heart rate (HR), noninvasive blood pressure (BP), oxygen saturation (SpO_2_), respiratory rate (RR), and partial pressure of end-tidal carbon dioxide (PetCO_2_). O_2_ at 2 L/min was applied through a nasal catheter, and intravenous access was opened. General anesthesia was induced with propofol (2 mg/kg), sufentanil (0.2 μg/kg), and cisatracurium (0.15 mg/kg). After adequate jaw relaxation was attained, tracheal intubation was performed, and each patient was mechanically ventilated with a tidal volume and ventilation rate adjusted to maintain the pressure of end-tidal carbon dioxide (ETCO2) at 35–45 mmHg. The anesthesiologist adjusted the intravenous speed of remifentanil and propofol according to hemodynamic parameters and BIS (BIS monitor; Aspect Medical System, Newton, MA). In the LBIS group, BIS was maintained between 40 and 50 during the operation, and in the HBIS group, BIS was maintained between 50 and 60 for maintenance. Both groups received 0.15–0.2 μg/kg/min for remifentanil and together with inhaled 50% air and 50% oxygen (O_2_) at a fresh gas flow rate of 2 L/min. Cisatracurium (0.05 mg/kg) was intermittently used for muscle relaxation. Ten minutes before the end of the surgery, stop all anesthetic infusions, and after extubating, the patients were transferred to the PACU for continuous monitoring.

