#### Strategies to improve adherence to interventions {11c}

The investigators will explain the treatment intervention in detail and supervise the compliance of the intervention throughout the entire procedure (during maintenance of anesthesia). Periodic monitoring will be conducted by a blinded investigators, for the recording of postoperative parameters and to ensure adherence to interventions.

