## Discussion

Dreams are a remarkable experiment in psychology and neuroscience, conducted every night in every sleeping person. They show that the human brain, disconnected from the environment, can generate an entire world of conscious experiences by itself. The occurrence of dreams is also one of the common phenomena of anesthesia and sedation. The occurrence of dreams during general anesthesia has been reported in the literature. The dream after anesthesia refers to the patient’s experience after the induction of anesthesia to the beginning of the waking phase. Domestic scholars have conducted research on the effects of short-town intravenous anesthesia and specific anesthetics on dreams of adult receiving surgery, which found that the incidence of adult dreams is about 18% ~ 49.7% [19, 20]. Among them, different anesthesia drugs, operation site, operation time, and so on are all the influential factors leading to the occurrence of dreams. Previous hypothesis also thought that dreaming occurs intraoperatively and is related to light or inadequate anesthesia [21, 22]. In order to verify this previous hypothesis, we designed a randomized, observer- and patient-blinded, controlled clinical trial, which compared the effects of different maintenance doses of propofol on patients’ dreams and analyzed the related factors affecting dreams. A recent study has shown that depression and anxiety assessed by Beck anxiety/depression inventory can predict a negative dream during natural sleep [23]. Similarly, we assessed preoperative anxiety level to see if patients with different preoperative anxiety states were associated with different dreams generated during anesthesia. In our trial, the subjective outcomes including HADS, Ramsay scale, modified Brice questionnaire, and awareness classification will be assessed. In this way, the effect of different dose of propofol maintained during the surgery on the incidence of dreaming of patients will be evaluated from multiple perspectives.

Our study has some limitations. First, since all the patients were hospitalized, we only scored the preoperative anxiety during the perioperative period but did not evaluate the daily long-term psychological base state and the degree of dreaming under natural sleep. Second, the study was part of a single-center survey, multicenter survey still need to be studied.

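### The anaesthesiologist who titrates to the allocated BIS band is declared blinded to allocation, which the described design does not allow

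*Protocol article*

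**What the plan says.** All statements are in the Protocol article.

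- **Who is blinded (Randomization, study intervention, and blinding).** "The patients, attending anesthesiologists, surgeons, and data collectors were all blinded to patient group assignment". The same section says that "anesthesia was conducted by the same anesthesiologist and outcome assessments were carried out by another anesthesiologist, and both were blinded to the group allocation".
- **What separates the arms (same section).** "In the LBIS group, BIS was maintained between 40 and 50 during the operation, and in the HBIS group, BIS was maintained between 50 and" (the quote stops just before the upper limit of the second band, which is 60).
- **Who delivers it (Standardized anesthesia).** "The anesthesiologist adjusted the intravenous speed of remifentanil and propofol according to hemodynamic parameters and BIS".
- **How allocation is concealed (Randomization, study intervention, and blinding).** An investigator opened the envelope on the day of surgery and "prepared the study drug according to the allocated group and delivered it to the operating room wrapped with opaque paper". The next sentence reads: "The result of the group allocation was not opened until the time of data analysis".
- **Who checks adherence (Strategies to improve adherence to interventions).** "Periodic monitoring will be conducted by a blinded investigators". The stated purposes are the recording of postoperative parameters and adherence to the intervention.
- **How the trial is labelled.** The Abstract says double-blind. The Discussion says "we designed a randomized, observer- and patient-blinded, controlled clinical trial".

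**The concern.** The intervention is a target on a monitor, pursued by the person giving the anaesthetic. A declaration that this person was blinded cannot be squared with the task the protocol gives them.

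What is at stake is how the results will be judged. A reader who accepts the declaration will treat performance bias as controlled by blinding. In fact a provider who knows the arm could, without departing from the protocol, use remifentanil differently within its permitted range or handle emergence differently. Either could plausibly affect what patients recall and report at the interview on recovery. The main outcomes (dreaming, dream pleasantness, satisfaction, awareness class) rest on interview or judgement, so an accurate account of who was blinded matters more here than it would for a laboratory endpoint.

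**Working it through.** The point contains no figure to reproduce. It is checked by setting the statements side by side.

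1. **What is the allocation?** Both arms have the same induction drugs and doses, the same maintenance agents (propofol and remifentanil), the same remifentanil range of 0.15–0.2 μg/kg/min, the same gas mixture and the same rule for stopping infusions. The only stated difference is the BIS band, 40–50 against 50–60. To know a patient's band is to know the patient's arm.

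2. **Who must know the band?** Standardized anesthesia has the anaesthesiologist adjust the infusions by haemodynamics and BIS. Someone choosing a rate to keep BIS in 40–50 rather than 50–60 needs to know which is intended. The article describes neither a masked or offset display nor a second person who titrates.

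3. **Could the provider have worked to a common range?** Safety assessment gives 40–60 for both groups, which is the two bands taken together. An anaesthesiologist who knew only that range could be blind, but would have no instruction that separates the arms. Blinding would be kept and the intervention lost.

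4. **Could the wrapping do the work?** Opaque paper can hide the identity of a drug. Here the drugs are the same in both arms and no arm-specific preparation is described. The distinguishing feature is a number on the monitor, which paper does not cover.

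5. **When was the allocation known?** The section says that the envelope was opened on the day of surgery and that the allocation was not opened until analysis. The two can be reconciled if only the preparing investigator saw the result. Then nobody titrating at the bedside knew the target, and the intervention could not be delivered as described.

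6. **Can a blinded person judge adherence?** Adherence means staying in the allocated band. A blinded monitor can confirm that BIS was recorded and lay within 40–60, but cannot say whether it lay in the right half.

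7. **Which description fits?** The Discussion names observer and patient. The methods list adds the attending anaesthesiologists. Steps 1 to 5 rule out the addition and leave the Discussion's description as achievable.

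8. **How many patients?** The methods say that the same anaesthesiologist conducted every anaesthetic, so the problem applies to 62 + 62 = 124 patients.

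**The case against.** The strongest reply is that the safeguards that matter most for these outcomes do exist. Patients are under general anaesthesia and cannot observe their BIS band. Outcomes are assessed by a different anaesthesiologist, declared blinded, after orientation has returned. The remifentanil range and the timing of stopping the infusions are common to both arms. All of this stands, and it limits the point in several ways.

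- A reader might infer that the main source of bias is left wholly uncontrolled. The document does not support that. Separate roles and a blinded assessor are a barrier, and a wrong statement about the provider does not remove it.
- A reader might infer that the double-blind label is simply false. The Abstract does not list who is blinded, and patient plus assessor is one accepted meaning, consistent with the Discussion. The conflict is between the Discussion and the longer list in the methods.
- A reader might try to size the bias by supposing some misrecorded dream reports. Five in an arm of 62 would be 5/62 = 8.1 percentage points, but nothing in the article suggests that number. It would also illustrate an unblinded assessor, whereas the demonstrated error concerns the provider.
- A reader might fault the article for giving no rules on handover or on the assessor's access to the anaesthetic record. A condensed article may leave these to the full protocol. Trial status also says that recruitment has finished, so new interview rules would come too late for most or all patients.

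On adherence, it is fair to add that the section's first sentence has investigators who are not described as blinded supervise compliance. That softens the difficulty, but the next sentence still gives adherence to a blinded person as well.

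None of this reaches the central point: the article makes a positive statement about provider blinding that its own intervention rules out.

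**Conclusion.** The statement is wrong as written. Blinding of the treating anaesthesiologist is a declared property that the described design does not have, and the methods list of blinded parties conflicts with the Discussion. The sentences on wrapped drugs and on when the allocation was opened do not rescue it and need explaining themselves.

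The error covers one of the four groups listed as blinded, and all 124 patients. Its effect on the estimates cannot be quantified from the document. What changes is the claim the trial can make: performance bias by the provider is not controlled by blinding, while patient and assessor blinding may still hold.

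The conclusion assumes that no masked display, separate titrator or arm-specific preparation was used, since none is described. If one was, the remedy is to describe it.

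**What to change.** 1. Describe the trial throughout (Abstract, methods, Discussion) as patient- and outcome-assessor-blinded with an unblinded treating anaesthesiologist, and take the attending anaesthesiologists out of the list of blinded parties.
2. Acknowledge as a limitation that blinding does not control performance bias by the provider, for example in remifentanil use within its range or in the handling of emergence.
3. Reconcile the wrapped-drug sentence and the two statements on opening the allocation by reporting who knew the allocation, from when, and what the wrapping was meant to conceal. Because recruitment has finished, this should be an account of what happened, not a silent deletion.
4. State that adherence to the BIS band is judged by someone who knows the band and does not assess outcomes. If that was not so during the trial, say so.

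The cost is wording. The two anaesthesiologist roles already exist, so no new outcome assessor is needed. The trial gives up the claim that the provider was blinded.

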### Standardized anesthesia

All patients were instructed not to eat for 8 h or to drink for 4 h prior to procedures, and no preoperative drugs were administered. Routine monitoring devices were set up to monitor electrocardiogram, heart rate (HR), noninvasive blood pressure (BP), oxygen saturation (SpO_2_), respiratory rate (RR), and partial pressure of end-tidal carbon dioxide (PetCO_2_). O_2_ at 2 L/min was applied through a nasal catheter, and intravenous access was opened. General anesthesia was induced with propofol (2 mg/kg), sufentanil (0.2 μg/kg), and cisatracurium (0.15 mg/kg). After adequate jaw relaxation was attained, tracheal intubation was performed, and each patient was mechanically ventilated with a tidal volume and ventilation rate adjusted to maintain the pressure of end-tidal carbon dioxide (ETCO2) at 35–45 mmHg. The anesthesiologist adjusted the intravenous speed of remifentanil and propofol according to hemodynamic parameters and BIS (BIS monitor; Aspect Medical System, Newton, MA). In the LBIS group, BIS was maintained between 40 and 50 during the operation, and in the HBIS group, BIS was maintained between 50 and 60 for maintenance. Both groups received 0.15–0.2 μg/kg/min for remifentanil and together with inhaled 50% air and 50% oxygen (O_2_) at a fresh gas flow rate of 2 L/min. Cisatracurium (0.05 mg/kg) was intermittently used for muscle relaxation. Ten minutes before the end of the surgery, stop all anesthetic infusions, and after extubating, the patients were transferred to the PACU for continuous monitoring.

### Observation indicators {12}

#### General data

The following patient data were collected from the anesthetic records: age, gender, height, weight, body mass index (BMI), American Society of Anesthesiologists physical status (ASA), duration of falling asleep, duration of surgery, duration of anesthesia, duration of recovery to consciousness (time between withdrawal of drugs and orientation of patients to time, place, and person), and drugs used for anesthetic management. The Hospital Anxiety and Depression Scale (HADS) is a self-report questionnaire used to assess the anxiety and depression status of participants during the perioperative period (Fig. 2). We used the Japanese version of HADS in this study. HADS consists of two subscales: anxiety (HADS-A) and depression (HADS-D). Each score consists of 7 questions, ranging from 0 to 3 (each score is 0–21), depending on the probability of the psychological problem described. Patients with a score of 11 or higher can be classified as possibly significant [13, 14]. We evaluated HADS score of patients the day before surgery.

**Fig. 2 Fig2:**
[figure not shown]
Patient inclusion and exclusion algorithm

#### Intraoperative data

Mean arterial pressure (MAP) and HR of each patient were recorded at 5 min after entering the operation room (T0), after anesthesia induces to fall asleep (T1), at the end of the operation (T2), recovery from anesthesia (T3), and exiting from the operation room (T4). Record the total amount of propofol used during surgery.

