### Statistical analysis

#### Sample size

In this trial, according to the previous study [18], the total dose of propofol in the dream group was 337 ± 161 mg and by 259 ± 145 mg in the no dream group. Using a *t* test of two independent samples in PASS for calculation, the withdrawal rate is 20% to ensure that the results are statistically different (*α* = 0.05, 1-*β* = 0.8); therefore, each group requires 56 subjects. To improve the reliability of the trial, we will recruit a total of 124 patients, with 62 in each group.

The SPSS 20.0 statistical software (SPSS, Inc., Chicago, IL, USA) and GraphPad Prism 6.0 software were used for data analysis. Continuous data were tested for normality. Normally distributed data were summarized using mean and standard deviation and were compared using unpaired two-tailed *t*-tests. Skewed data were summarized using.median and range and were compared using Wilcoxon rank-sum tests. Categorical data were summarized using number (%) and were compared using *Χ*^2^ test or Fisher’sexact tests. Logistic regression was used to determine predictors of dreaming and correlation with dream quality. Categorical variables were created from continuous variables in applicable cases. A *P* value of less than 0.05 was considered statistically significant.

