#### Methods in analysis to handle protocol non-adherence and any statistical methods to handle missing data {20c}

All researchers will be trained referring to the same training protocol. Missing intraoperative data, if any, will be obtained from the electronic hospital files. Postoperative evaluation at specified time points is mandatory, and missing postoperative data are not to be anticipated. Analyses of all outcomes will be performed according to the intention-to-treat principle, and once enrolled, all participants will be analyzed, regardless of the findings.

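### The five listed MAP and HR readings miss the maintenance period in which the BIS targets differ, so they do not directly measure the haemodynamic effect of the target (minor)

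*Protocol article*

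**What the plan says.** All references are to the protocol article.

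- **Intraoperative data.** MAP and HR "were recorded at 5 min after entering the operation room (T0"), then "after anesthesia induces to fall asleep (T1), at the end of the operation (T2), recovery from anesthesia (T3"), and finally on "exiting from the operation room (T4"). No other MAP or HR reading is listed.
- **Standardized anesthesia.** One induction regimen is given for everyone: "General anesthesia was induced with propofol (2 mg/kg), sufentanil" and cisatracurium follow by weight. The arms separate afterwards. The low group is held at BIS 40 to 50, while "in the HBIS group, BIS was maintained between 50 and 60 for maintenance". Propofol and remifentanil are adjusted to haemodynamic parameters as well as to BIS, in both arms. Near the end: "Ten minutes before the end of the surgery, stop all anesthetic infusions".
- **Statistical analysis** (text under Sample size). Normally distributed continuous data "were compared using unpaired two-tailed" t-tests, and skewed data by Wilcoxon rank-sum tests. No baseline term is mentioned.
- **Section on non-adherence and missing data {20c}.** "Missing intraoperative data, if any, will be obtained from the electronic hospital files". The General data section also draws on the anaesthetic records.
- **Conclusion.** The aims are dream incidence, awareness, pleasant dreams, propofol dose and factors associated with dreaming. No haemodynamic aim is stated.

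**The concern.** MAP and HR are the only physiological series listed as intraoperative data, yet the schedule passes over the part of the operation in which allocation changes what the patient receives. A table of T0 to T4 by arm with no differences could easily be taken to mean that the two BIS targets are haemodynamically alike. The readings do not bear on that directly.

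The gap also touches the propofol dose comparison, which is one of the stated aims. Haemodynamics during maintenance help to set the propofol rate, so those values would help in interpreting a dose difference, and they are the ones not listed.

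A smaller matter is that T0 is collected before treatment differs and is a natural covariate for the later readings, but the methods named for continuous data do not use it.

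**Working it through.** **Step 1: place each reading against the contrast.** The protocol gives no target difference, SD or power for MAP or HR, so there is no figure of its own to reproduce. The check begins with the timeline.

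| Reading | When | Relation to the BIS contrast |
|---|---|---|
| T0 | 5 min after entry | before induction |
| T1 | after falling asleep | after the common induction, before maintenance |
| (none) | maintenance | arms held at 40-50 and 50-60 |
| (none) | 10 min before end of surgery | infusions stopped |
| T2 | end of operation | about 10 min after the stop |
| T3 | recovery | later |
| T4 | leaving theatre | later |

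Two readings come before the contrast, three come after the infusion stop, and 0 of 5 fall in between.

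**Step 2: what the timing could cost.** How much of a maintenance difference survives to T2 is not given, so a range is needed. Assume a true maintenance difference of 0.5 SD, of which a fraction f remains at T2. With 62 per arm and two-sided alpha 0.05, counting the tail in the direction of the effect:

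power = Φ( 0.5f / √((1 − r²) × 2/62) − 1.960 ), with √(2/62) = 0.1796

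Here r is the correlation of the reading with T0, and r = 0 gives the unadjusted test. For f = 1 and r = 0: 0.5/0.1796 − 1.960 = 0.824, and Φ(0.824) = 0.795.

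| Fraction retained at T2 (assumed) | Unadjusted | Adjusted for T0, r = 0.5 (assumed) |
|---|---|---|
| 100% | 80% | 90% |
| 75% | 55% | 67% |
| 50% | 29% | 36% |
| 25% | 10% | 12% |
| 0% | 2.5% | 2.5% |

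Most of the loss comes from timing. Adjustment helps if an effect persists, but it cannot recover one that has gone.

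**Step 3: what T0 adjustment gains.** Residual variance is multiplied by 1 − r²:

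- r = 0.5: 1 − 0.25 = 0.75, a 25% reduction.
- r = 0.7: 1 − 0.49 = 0.51, a 49% reduction.

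The difference detectable with 80% power is (1.960 + 0.842) × √(2(1 − r²)/62):

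- r = 0: 2.802 × 0.1796 = 0.50 SD
- r = 0.3: 0.50 × √0.91 = 0.48 SD
- r = 0.5: 0.50 × √0.75 = 0.44 SD
- r = 0.7: 0.50 × √0.51 = 0.36 SD

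All correlations are assumed. Under 1:1 randomization the unadjusted comparison remains unbiased, so the gain is in precision alone.

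**The case against.** The strongest reply is that the trial never sets out to estimate a haemodynamic effect. MAP and HR are listed as observations at the usual landmarks of an anaesthetic, with no hypothesis attached, and wanting maintenance readings as well is a preference. That stands in part: the dreaming comparison is untouched and the point can only be minor. What remains is the risk of misreading the T0 to T4 table.

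Second, maintenance readings would themselves be hard to interpret. Drugs are titrated to haemodynamics in both arms, and hypotension and bradycardia are treated as they arise, so the contrast would be blunted even if read at the right time. This stands, and it limits any maintenance comparison to a supportive role. The adverse event form, which records time, duration and severity, also gives another route by which clinically relevant events are captured.

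Third, covariate adjustment of a secondary series is often left to an analysis plan, and none is shown. For that reason its absence is not counted as an error here. Adjustment is offered as an inexpensive gain, since the only methods the article names are unadjusted.

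Fourth, the {20c} section uses electronic files to fill missing intraoperative data but does not say that they hold serial MAP and HR. That also stands, and availability has to be confirmed.

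**Conclusion.** The timing point holds on the text alone: none of the five listed readings samples maintenance, so they do not directly measure the haemodynamic effect of the BIS target. A result of no difference is not evidence of equivalence during maintenance. How much sensitivity is lost at T2 depends on an unknown retained fraction. For an assumed 0.5 SD effect, unadjusted power runs from 80% with full carry-over to 2.5% with none.

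A reader might infer three stronger things that the documents do not support:

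- *That the series cannot show any effect, whatever happened in maintenance.* T2 is only about ten minutes after the infusions stop, so a residual difference is possible. The documents do not say how large.
- *That ten tests are planned, four of which can be significant only by chance.* Two variables at five times would make ten, but the article's wording on continuous data is generic. It does not say that each time point is tested, or that T0 and T1 are tested at all.
- *That leaving out T0 invalidates the comparison.* In a randomized comparison it costs precision and causes no bias.

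Priority is minor, and the dreaming comparison is unaffected.

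**What to change.** 1. Compare MAP and HR at T2, T3 and T4 by ANCOVA with the T0 value as covariate. This needs no new data.
2. Report T0 and T1 by arm descriptively, labelled as values before the contrast.
3. Check whether the anaesthetic records or electronic files hold MAP and HR during maintenance. If they do, abstract the mean and lowest value for each patient from the start of maintenance to the infusion stop. Compare the arms on these as a supportive analysis, stating that both arms were titrated to haemodynamics.
4. If the readings are not available, say that T0 to T4 do not cover maintenance and draw no haemodynamic conclusion about that period.

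The cost is a change of model and a small amount of data abstraction by staff blind to allocation. No new procedure is needed and patient care does not change. The Trial status section says recruitment is finished and data collection continues, so the reading schedule can no longer be altered, but abstraction may still be possible. The choice should be fixed before allocation is disclosed for analysis.
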